## Abstract

**Background:**

Assam, India, has the country’s highest maternal mortality ratio (195 per 100,000 live births), mainly due to poor access to and quality of maternal health (MH) care. Many women receive inadequate antenatal and postnatal services, made worse by isolation, socioeconomic barriers, and weak health care infrastructure. Digital tools like mobile messaging and chatbots have improved antenatal care (ANC) and facility-based deliveries in similar settings. The e-SAATHI (Strengthening ANC/PNC via AskNivi Tailored Health Information, Referrals, and Follow-Up) project aims to provide personalized, stage-specific maternal health support through a chat-based system in Assam.

**Objective:**

This study assesses the acceptability, feasibility, and effectiveness of the e-SAATHI chatbot in increasing women’s access to MH information and improving ANC and PNC service uptake across public and private facilities. Objectives include increasing ANC/PNC use (eg, ≥4 ANC visits and timely PNC), promoting respectful care, and gathering insights for scaling digital health in high-burden regions.

**Methods:**

Phase 1 (0‐3 mo) involves co-designing and pilot testing aligned with World Health Organization and national guidelines. Phase 2 (4‐24 mo) involves enrolling pregnant and postpartum women via health facilities and social media. The chatbot sends 2-3 messages weekly from 10-week pregnancy to 15 weeks postpartum. About 300 health care providers will be trained and engaged for onboarding and feedback. Phase 3 (25‐36 mo) involves scaling up across districts, reaching 225,000 women. Data collection includes interviews, surveys, facility assessments, and chatbot analytics. Qualitative analysis will explore experiences; quantitative data (ANC completion, facility delivery, PNC follow-up, and satisfaction) will compare pre- and post-interventions. Ethical approvals, informed consent, and data confidentiality are observed.

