Sample size	10 from range of facility levels periodically	2‐4 women per facility—periodically	200 PN women	Each facility taking part in the project	All women who use chatbot
Location of activity	Private room at health facility or mutually agreed site	Private room at health facility or mutually agreed site	Recruitment at PNC^e^ ward then short interview (2‐8 wk later)	Facility level data (deidentified)	Online program data
Timing	Baseline and periodically 6‐9 mo	Baseline, midline, and endline	Baseline, then periodically (9 mo after chatbot introduction)	Quarterly	From initiation of chatbot to end of project
Method	In-depth face-to-face interview by researcher	In-depth face-to-face interview by researcher	Short in-person/telephone survey by researcher	Facilities visited by researcher	Analysis of chatbot program data

a Analysis of baseline, midline, and endline data will occur after the completion of each respective phase; interim analyses will be performed after midline (2026) and final analyses after endline (2027).

b IDI: in-depth interview.

c PN: postnatal.

d MH: maternal health.

e PNC: postnatal care.

First, this includes any MH provider (at least 10) over 18 years, who consent to be interviewed and work in one of the public or private facilities in the study areas, nurses, midwives, auxiliary nurse midwives, Accredited Social Health Activists (ASHAs), and doctors at health facilities engaged in the digital MH support system. The purpose of the interviews with MH providers is to identify facility and provider-specific issues that may affect the delivery of care and uptake of women onboarding onto the chatbot. Researchers will use a short in-depth interview (IDI) guide to ask respondents about their expectations regarding the MH chatbot, its strengths and weaknesses, develop an in-depth understanding of the process of introducing the chatbot, and how it might be improved and subsequently scaled up. Data will be analyzed iteratively after each collection wave to inform ongoing implementation and comprehensively the completion of phase 2.

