Second, this will be conducted with a subsample of women (n=10) who used the MH chatbot and accessed its services in a facility. These interviews will be used to gain a deeper understanding of the motivations, perceptions, and priorities of women using the chatbot and facility services. Researchers will use a short IDI guide to ask respondents on their experience of using the MH chatbot, its strengths and weaknesses, and how it might be improved. Women will be at least 18 years old, have consented to the interview, and have given birth in a facility within the preceding 6 months. Data will be analyzed iteratively after each collection wave to inform ongoing implementation and the comprehensive completion of phase 2.

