Third, postnatal women who have given birth and have experienced MH journey and/or used *askNivi* chatbot (>18 y age) will be approached in a postnatal ward at a facility. Women who consent to participate will be contacted telephonically between 2 to 8 weeks after the date of delivery for a telephonic or in-person survey. The study team will note their identifying information for future contact separately from the data. During the recruitment or enrollment at the facility, the research assistant will ask permission to contact the woman. A member of the study team will call and agree on a time that suits them. That same member of the team will then call to interview at the conveniently decided time. The short dipstick survey will cover the quality of care, experiences during pregnancy (number of ANC contacts, etc), childbirth and postnatally, and experience of using askNivi chatbot. Women who had loss or severe complications during childbirth were excluded. We will use the dipstick survey parameters field feedback to modify/adapt the composite quality score of maternal and newborn care as a composite measure designed to assess the quality of maternal and newborn health services received [24]. Each indicator will be scored based on whether the recommended standard will be met, typically using a binary (yes/no) scale. The scores for all indicators will then be summed to produce a total score, which will often be standardized to a percentage for ease of interpretation. This approach will allow for comparison of service quality across facilities and overtime and will help identify specific areas for improvement [24]. Quantitative analyses will be conducted after baseline, midline, and endline data collection points. Data cleaning and quality checks will occur fortnightly during collection with a comprehensive pass before midline and endline analyses.

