Fourth, a short checklist including facility staffing levels; maternity unit capacity, medicines, supplies, and infrastructure; educational materials, job aids and protocols; health management information system and information and communication technology; facilitation and management of emergency referrals and transport; and other MH interventions available in the facility. This checklist will be administered to the in-charge or delegate of the facility. Statistics related to routine program data on utilization or uptake of maternal and newborn health services (ANC, PNC, births, and deaths) will be collected. Monthly trends in the numbers of new and continuing ANC and PNC clients will be obtained from facility records.

Fifth, this includes responses from women who have joined the MH chatbot (e-SAATHI), including demographic information and use of services. The data used is from all women who interact with the MH platform. Women who are on board with the chatbot permit their data to be used (deidentified).

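### Facility delivery is named as a pre-post outcome, but the survey recruits on facility postnatal wards and no described source gives a pre-post proportion; only birth numbers can be tracked

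*Protocol article*

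**What the plan says.** The Methods paragraph of the abstract names the outcome: "quantitative data (ANC completion, facility delivery, PNC follow-up, and satisfaction) will compare pre- and post-interventions". The body does not repeat facility delivery by name. Under Quantitative Analysis it lists uptake of services as a group of secondary outcomes, to be compared between baseline and follow-up, and the data source that section describes is the postnatal women's (dipstick) survey.

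On who enters that survey, Monitoring and Iterative Improvement says that postnatal women "will be approached in a postnatal ward at a facility". Table 1 agrees: recruitment is on the postnatal ward, with the interview 2 to 8 weeks later, at baseline and then periodically.

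Three other sources could bear on place of birth:

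- **In-depth interviews with women.** These women must "have given birth in a facility within the preceding 6 months". The subsample is 10 and the analysis is qualitative.
- **Routine facility data.** "Statistics related to routine program data on utilization or uptake of maternal and newborn health services (ANC, PNC, births, and deaths) will be collected". Table 1 gives the timing as quarterly. A further sentence promises monthly figures, but for other items: "Monthly trends in the numbers of new and continuing ANC and PNC clients will be obtained from facility records".
- **Chatbot platform data.** These are "responses from women who have joined the MH chatbot (e-SAATHI), including demographic information and use of services". Table 1 says they run from the start of the chatbot to the end of the project.

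**The concern.** A survey that recruits on a facility postnatal ward conditions on the event it is meant to measure. A woman who gave birth at home, and was not admitted afterwards, cannot be approached. The facility-delivery proportion is then fixed by the sampling and carries almost no information about the chatbot. Adjustment for clustering and confounders, which the article plans, cannot restore variation that recruitment removed.

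This matters because the second objective is the chatbot's effect on uptake of services, and the Implementation section names encouragement of facility births as one way the chatbot should work. A flat result near 100% in both periods could be read as no effect, or as full coverage, when it is neither.

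The same selection touches the survey's antenatal and postnatal care results. They describe women who delivered in participating facilities. If the mix of women who deliver there changes, those results can move although no woman's care has changed.

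**Working it through.** The article gives no facility-delivery rate, sample-size calculation or power, so there is no stated figure to reproduce. The check goes source by source.

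**1. The survey.** Input: 200 postnatal women (Table 1). The table does not say whether that is per wave or in total; I take 200 per wave. If every woman on the ward delivered in a facility:

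- baseline 200/200, follow-up 200/200;
- difference = 100% − 100% = 0; Fisher's exact P = 1.0; odds ratio undefined; the power formula fails because the variance is zero.

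The 100% is not strictly guaranteed, since a woman admitted after a birth elsewhere could be on the ward. Suppose a share q of baseline ward women delivered elsewhere and none did at follow-up, which is the most favourable change possible. With 200 per wave and a two-sided 0.05 level (sidedness assumed), Fisher's test needs at least 6 such women against 0: 6 against 0 gives P = 0.030, and 5 against 0 gives P = 0.061. Exact power is therefore P(X ≥ 6) for X ~ Binomial(200, q):

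| Assumed q | Expected number, 200 × q | Exact power | Normal approximation |
|---|---|---|---|
| 0.5% | 1 | 0.06% | 16% |
| 1% | 2 | 1.6% | 29% |
| 2% | 4 | 21% | 51% |

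The normal approximation (follow-up rate set at 99.99%) is too generous at such small counts. On either method the comparison is close to uninformative. Even a detected change would concern admissions after birth elsewhere, not the share of all women who deliver in a facility.

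**2. Routine facility data.** These count births in the facility, and no count of births elsewhere is described. A count does not identify a share. With assumed figures, facility births rising from 800 to 880 fit both of these:

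- share unchanged: 0.80 × 1,000 = 800, then 0.80 × 1,100 = 880;
- share up: 0.80 × 1,000 = 800, then 0.88 × 1,000 = 880.

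**3. Chatbot data.** Subscribers can join through social media, so they are not limited to facility births. But the data begin with the chatbot, so there is no pre-intervention period. The article mentions use of services and does not say whether place of birth is recorded.

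**4. Interviews with women.** Facility birth is an entry condition, and the data are qualitative.

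**5. Effect on antenatal care results.** Let p0 be the proportion with at least 4 antenatal visits among women who would deliver in the facility anyway, p1 the proportion among women newly drawn in, and w the newcomers' share of the follow-up sample. The measured proportion is (1 − w) × p0 + w × p1, a shift of w × (p1 − p0). All inputs are assumed; p0 = 50% echoes the population figure in the Introduction and may not hold for ward women. With p1 = 20%:

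- w = 5%: 0.95 × 50% + 0.05 × 20% = 48.5%
- w = 10%: 0.90 × 50% + 0.10 × 20% = 47.0%
- w = 15%: 0.85 × 50% + 0.15 × 20% = 45.5%

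If p1 exceeds p0 the shift is upward, so the direction is not known in advance.

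**The case against.** The strongest reply has four parts.

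*The abstract does not assign facility delivery to the survey.* It follows a list of four kinds of data, and an article may leave the mapping of indicator to source to the full protocol. This stands as far as it goes. But none of the sources as described can supply a pre-post proportion, so the problem does not depend on which one was meant.

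*Facility birth counts can show a change.* Correct. A reader might infer that no listed source can show any change in facility delivery. The documents do not support that: births are among the routine statistics, and their number can be followed over time. What is missing is a denominator.

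*The outcome is minor.* Also correct. Facility delivery is named as an outcome only in the abstract and belongs to the secondary uptake indicators. Nothing here invalidates the primary composite quality score.

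*A facility-based sample suits the aim, which concerns services in public and private facilities, and the limitations are already conceded.* This is partly right. The ward sample is reasonable for quality of care. But the Limitations section discusses secular trends and differences between women who can and cannot use the chatbot; it does not say that the survey is conditioned on facility birth.

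Two further readings go too far. A difference of exactly zero is not guaranteed, because a ward can hold women who delivered elsewhere. And the fall from 50% to 47% in antenatal care is not a prediction: its inputs are assumed and its sign could reverse.

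**Conclusion.** The concern holds in a limited form. As described, the plan cannot deliver a pre-post comparison of the proportion of women delivering in a facility. In the survey the outcome is at or near its ceiling by design: the difference is 0 if all ward women delivered in a facility, and exact power is at most about 21% if as many as 2% at baseline had delivered elsewhere and none later. Routine data support a statement about numbers of facility births only, and chatbot data have no baseline.

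The conclusion rests on the recruitment text and Table 1 as printed, and on the absence of any described count of births outside facilities. The power figures also assume 200 women per wave, no clustering and a two-sided test. The shift in the antenatal care results is a possible consequence of unknown size and direction.

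**What to change.** 1. Do not analyse facility delivery as a pre-post proportion from the survey. Report it as the number of births per facility from the routine data, which Table 1 schedules quarterly, and label it a volume measure that cannot show a change in share.
2. If the chatbot records place of birth, report it among subscribers, descriptively only. The article does not establish that it is recorded, so this needs confirming first.
3. State that survey results on antenatal and postnatal care apply to women who deliver in participating facilities, and that a change in who delivers there could shift these results in either direction.

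The first and third changes cost only wording and can be made before the final analysis in 2027. The price is one fewer uptake outcome and a narrower stated conclusion.

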**Results:**

The study was funded in September 2022. As of August 2025, 210 facilities have been onboarded, and 201,813 women were enrolled. Chatbot-based data collection began in April 2023 and will continue through the study period. Qualitative and quantitative evaluation data collection started in November 2023 and is expected to complete in June 2027. Interim analyses will be conducted after midline data collection in 2026; final analyses will be performed after endline data collection in 2027. The primary outcome will be the change in the composite quality score of maternal and newborn care. Secondary outcomes will include service uptake indicators, user-reported knowledge and self-care practices, and satisfaction with care. Operational feasibility—including provider integration and barriers such as digital literacy and connectivity—will also be assessed. Ongoing collaborative learning and adapting cycles are expected to capture intervention adaptations and inform optimal strategies for scale-up.

**Conclusions:**

e-SAATHI offers a scalable digital approach to improve MH across a variety of sociodemographic, linguistic, and risk settings. By delivering timely, personalized support, the chatbot may enhance health-seeking behavior and outcomes in Assam and in similar low-resource areas globally.

## Introduction

Despite decades of investments and initiatives to address intergenerational and deep-rooted social and cultural norms around maternal health (MH), progress has been slow in selected geographies of India, such as Assam. The state records the highest maternal mortality ratio in the country, nearly double the national average of 195 per 100,000 live births (2018‐2020) compared to 103 per 100,000 live births in (2017‐2019) [1-3]. Key indicators reflect significant gaps in care quality and utilization—only half of pregnant women receive the recommended 4 or more antenatal care (ANC) visits—approximately 48% received postnatal care (PNC) from trained health personnel, and, among Janani Suraksha Yojana beneficiaries, only 45% of newborns initiated breastfeeding within the critical first hour [4,5].

The persistently high maternal mortality rate in Assam stems from multiple interconnected factors [6,7]. Geographic barriers limit health care access, while socioeconomic challenges compound these difficulties [6,8]. The public health system faces an overwhelming delivery burden insufficiently coordinated with private MH providers [9]. Gaps include limited access to personalized pregnancy and childbirth information, inadequate self-care guidance, low insurance coverage, and high out-of-pocket expenditures [8,10,11]. Women’s restricted autonomy further constrains their access to, and use of, quality reproductive and MH services—collectively contributing to poor health outcomes for mothers and newborns [8,12]. While India has achieved a notable decline in maternal and newborn mortality over the past 2 to 3 decades, partly attributable to various maternal and newborn health policy reforms, significant challenges remain, particularly in high-burden states like Assam [6,7].

Direct-to-beneficiary mobile health (mHealth) programs that provide stage-based health information to new and expectant mothers have proliferated rapidly over the last decade [13]. In low-income and middle-income countries (LMICs), mHealth messaging programs represent some of the most successful examples of digital health programs, demonstrating measurable improvements in MH services [13,14]. Several digital MH services have achieved significant scale in Bangladesh, India, South Africa, and Tanzania, with each program reaching over 1 million subscribers and demonstrating potential for population-level impact [13,15].

The Government of India has prioritized digital health initiatives, leveraging the fact that more than 3-quarters of men and two-thirds of women own a mobile phone [16]. Smartphone ownership reaches approximately half of men (49%) and just over a quarter of women (26%) with notable variation between urban and rural settings.

Digital platforms and mHealth apps offer significant potential to improve the health information delivery and service access, even in contexts with low literacy levels [17-19]. Most digital health interventions use telephone-based systems that can engage individuals in their everyday lives, help them navigate into and across the health system, and capture client feedback following provider interactions.

Evidence demonstrates that messaging systems using digital apps or chatbots positively impact key MH indicators, including improved attendance at 4 or more ANC visits and increased facility-based deliveries [20-22].

This protocol paper describes the e-SAATHI (*Strengthening Antenatal Care/Postnatal Care via AskNivi Tailored Health Information, Referrals, and Follow-Up*) project—an iterative, collaborative learning and adapting (CLA) approach to document and monitor the introduction and scale-up of a chat-based digital support system (askNivi) for pregnant and postnatal women residing in the state of Assam, India, throughout their MH journey. Using WhatsApp, health information messages are sent to pregnant and postnatal women weekly based on the World Health Organization (WHO) guidelines during pregnancy and up to 15 weeks postnatally. The e-SAATHI project also identifies public and private MH providers to engage with the chatbot—to provide quality services to pregnant and postnatal women.

## Methods

### Aim and Objectives

The main aim of e-SAATHI is to evaluate the effectiveness of designing, implementing, and evaluating a digital health approach (chatbot) for improving women’s access to MH information and quality services in public and private health facilities in the state of Assam.

Key objectives are as follows: (1) to assess the acceptability and feasibility of an MH chatbot approach in increasing access/uptake of respectful MH services in public and private facilities; (2) to design, implement, monitor, and evaluate the effect of MH chatbot to improve the uptake of services; and (3) to document and assess the dynamics of implementing interventions to introduce an MH chatbot and generate lessons for replication/expansion at scale.

### Population

Our geographic target area is in Northeast India in the demographically and topographically diverse state of Assam where progress in improving key MH indicators has stalled and interventions are required to accelerate toward sustainable development goal targets. Given the challenges that Assamese pregnant women face regarding equitable access to timely, respectful, and quality MH care across geography and socioeconomic strata, a weak and overburdened public health system, and an underutilized private health sector, the e-SAATHI project intends to adapt, test, and scale a digital marketplace approach (chat-based digital support system: askNivi). Respectful maternity care is defined by WHO as care organized for and provided to all women in a manner that maintains their dignity, privacy, and confidentiality, ensures freedom from harm and mistreatment, and enables informed choice and continuous support during labor and childbirth [23]. This project will be implemented in up to 10 districts in the state of Assam, with a total of 300 health care facilities. Initially, 5 facilities will be brought on board, followed by additional facilities in 3 districts and finally facilities across 10 districts by the end of 3 years. For monitoring and evaluation purposes, care providers and users will both be participants for the qualitative work, while the chatbot users will be part of the quantitative dipstick surveys.

